##### Probability trade-off

Interviewers will undertake probability trade-off exercises with "ping-ponging" to determine participant thresholds for accepting LMWH prophylaxis [73,74]. We will use a scenario based on the absolute effects of LMWH versus no prophylaxis for prevention of recurrent VTE during nine months of pregnancy. The interviewer will systematically vary the risk of VTE with LMWH prophylaxis (alternating between high and low risks) to determine the minimum acceptable reduction in the risk of VTE with prophylaxis at which the participant would agree to initiate LMWH. Based on the 95% CI surrounding the incidence of antepartum VTE in high risk patients reported in the prospective cohort study [9], we estimate that the upper bound of risk of recurrent VTE is 16 out of 100 without prophylaxis. Therefore, we will set this risk fixed on one side of the flipchart and will start offering probabilities ranging from 16 fewer VTE events per 100 pregnancies (maximum absolute risk reduction) to 0 less VTE events (same VTE risk as no prophylaxis) on the other side of the chart.

##### Visual analog scale (feeling thermometer)

Interviewers will determine the value patients place in relevant health states using a visual analog scale called the Feeling Thermometer (FT) [75]. When making ratings using the FT, women choose the score on the thermometer that represents the value they place on the health state they are evaluating. The FT is anchored at death (0) and full health (100). We will ask participants to consider (i) the health state of pregnancy with LMWH prophylaxis using the standard description or their previous experience (for those with two weeks or more of prophylactic LMWH during pregnancy), (ii) a pregnancy with their own most recent VTE experience, (iii) a standardized health state with a pregnancy-related DVT, (iv) a standardized health state with a pregnancy-related PE and (v) a standardized health state representing an obstetrical bleed (Additional file 1: Appendix I).

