**Methods:**

We will perform a multi-center cross-sectional interview study in Canada, USA, Norway and Finland. The study population will consist of 100 women with a history of lower extremity deep vein thrombosis (DVT) or pulmonary embolism (PE), and who are either pregnant, planning pregnancy, or may in the future consider pregnancy (women between 18 and 45 years). We will exclude individuals who are on full dose anticoagulation or thromboprophylaxis, who have undergone surgical sterilization, or whose partners have undergone vasectomy. We will determine each participant's willingness to receive LMWH prophylaxis during pregnancy through direct choice exercises based on real life and hypothetical scenarios, preference-elicitation using a visual analog scale (“feeling thermometer”), and a probability trade-off exercise. The primary outcome will be the minimum reduction (threshold) in VTE risk at which women change from declining to accepting LMWH prophylaxis. We will explore possible determinants of this choice, including educational attainment, the characteristics of the women’s prior VTE, and prior experience with LMWH. We will determine the utilities that women place on the burden of LMWH prophylaxis, pregnancy-related DVT, pregnancy-related PE and pregnancy-related hemorrhage. We will generate a “personalized decision analysis” using participants’ utilities and their personalized risk of recurrent VTE as inputs to a decision analytic model. We will compare the personalized decision analysis to the participant’s stated choice.

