Finally, we will perform a “personalized decision analysis” for each woman in the study. We will update a prior decision analytic model examining prophylactic LMWH in pregnant women with a history of prior VTE (Figure 4) [87], using each women’s visual analog scale utility assessments for the relevant outcomes of DVT in pregnancy, PE in pregnancy, obstetrical hemorrhage and the burden of LWMH prophylaxis in pregnancy. Given that the risk of heparin-induced thrombocytopenia (<0.1%) and heparin associated osteoporosis (<1%) are either not increased or minimally increased with prophylactic LMWH [65,68], we will not consider these health states in the decision analysis. We will place the health state utilities in the decision model for each woman’s current situation and the three hypothetical scenarios. We will compare the decision model’s results with the VTE threshold selected in the probability trade-off tasks.

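### No rated health state is an uncomplicated pregnancy without LMWH, so a woman's own ratings cannot isolate the LMWH burden that the personalized decision model needs

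*Protocol article*

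**What the plan says.** The protocol article's section on the visual analog scale sets the scale: "The FT is anchored at death (0) and full health (100"). It then lists what each woman rates. The first item is "i) the health state of pregnancy with LMWH prophylaxis using the standard description or their previous experience". The second places her own latest VTE in a pregnancy. Two more are scripted descriptions, one of DVT and one of PE, and the last is "v) a standardized health state representing an obstetrical bleed". The Outcomes section also counts five states, so the list is closed. There the first rating is described as the burden of using LMWH in pregnancy.

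Under Analysis, Primary and secondary outcome(s), an earlier decision model is to be updated with each woman's own ratings of DVT, PE, "obstetrical hemorrhage and the burden of LWMH prophylaxis in pregnancy". The model is run for her current situation and for the three hypothetical scenarios. That section compares the model's "results with the VTE threshold selected in the probability trade-off tasks". The Methods part of the Abstract names a different comparator: "We will compare the personalized decision analysis to the" choice that the participant stated.

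**The concern.** Every rated state is a treated or complicated pregnancy. The state that most women in the no-prophylaxis branch would occupy, an uneventful pregnancy without injections, is not rated. The rating of pregnancy with LMWH mixes two things: what the woman deducts for being pregnant and what she deducts for LMWH. Only the second is the burden of LMWH, and the five ratings do not separate them.

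The model still needs a value for the uneventful, untreated branch. If full health (100) is used, any deduction for pregnancy falls on every woman in the LMWH arm but only on women with an event in the other arm. If a constant from outside is used, the burden is no longer the woman's own. Either way, disagreement between the model and the woman could partly reflect the missing reference rather than her values.

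The comparison has a second problem. A preferred option in four situations and a single threshold elicited at a fixed baseline of 16 per 100 are different quantities, and the Abstract and the Analysis section do not name the same one.

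**Working it through.** **The plan's own figures.** Table 3 applies a 70% relative risk reduction: 4 × 0.30 = 1.2, 10 × 0.30 = 3.0 and 16 × 0.30 = 4.8, which round to the stated 1, 3 and 5 per 100. Women without an event in the no-LMWH column number 100 − 4 = 96, 100 − 10 = 90 and 100 − 16 = 84 per 100. (The table prints 10 for the middle figure, which does not fit its own risk of 10 per 100; 90 is used here.)

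**Model for the check.** This is a one-period tree, simpler than the planned Markov model and without bleeding. Let r0 and r1 be the VTE risks without and with LMWH, L the rating of pregnancy with LMWH, V that of pregnancy with VTE, and ref the value of an uneventful pregnancy without LMWH.

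- EU(LMWH) = r1·V + (1 − r1)·L
- EU(no LMWH) = r0·V + (1 − r0)·ref
- Setting them equal gives the break-even reduction: r0 − r1 = (1 − r0)(ref − L)/(L − V)

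**Assumed ratings** (the article gives none): uncomplicated pregnancy P = 90, L = 88, V = 40. The true LMWH increment is 2 points.

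Break-even at r0 = 0.16:

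- ref = 90: 0.84 × 2/48 = 0.035, or 3.5 fewer VTE per 100
- ref = 100: 0.84 × 12/48 = 0.210, or 21.0 fewer VTE per 100, outside the 0 to 16 range of the trade-off

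The inflation is the ratio of the two burdens, (100 − L)/(P − L) = 12/2 = 6.

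EU(LMWH) − EU(no LMWH) in the Table 3 scenarios:

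| Scenario | ref = 90 | ref = 100 |
|---|---|---|
| 4 to 1 per 100 | 87.52 − 88.00 = −0.48 | 87.52 − 97.60 = −10.08 |
| 10 to 3 per 100 | 86.56 − 85.00 = +1.56 | 86.56 − 94.00 = −7.44 |
| 16 to 5 per 100 | 85.60 − 82.00 = +3.60 | 85.60 − 90.40 = −4.80 |

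The preferred option changes in two of the three scenarios.

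**Range over assumptions.** LMWH increment 1, 2 or 5 points; VTE 30 or 50 points below uncomplicated pregnancy; break-even per 100 at the 16 per 100 baseline:

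| Uncomplicated pregnancy rated | Own rating as reference | Full health as reference |
|---|---|---|
| 100 | 1.7 to 16.8 | 1.7 to 16.8 |
| 95 | 1.7 to 16.8 | 10.3 to 33.6 |
| 90 | 1.7 to 16.8 | 18.9 to 50.4 |
| 80 | 1.7 to 16.8 | 36.0 to 84.0 |

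With the woman's own reference, the result does not depend on how she rates pregnancy itself. With full health it depends on it heavily.

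**Outside constant.** Suppose 92 is used for everyone. A woman who rates pregnancy with LMWH at 95 then has a burden of 92 − 95 = −3, a benefit from the injections that she never expressed.

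**Comparator.** The model is run at the woman's own risk and at 4, 10 and 16 per 100. The trade-off fixes the untreated risk at 16 per 100. Of the three scenarios, only the last shares that baseline.

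**The case against.** A reader might infer that the planned model charges pregnancy itself to LMWH and is biased against it. The article does not support that as a statement of fact. It nowhere says that the burden is 100 minus the rating. The model updates an earlier one that may carry its own value for an uneventful pregnancy; the model figure and the appendix with the state descriptions are not shown. The bias also needs women to rate uncomplicated pregnancy below 100. The Background notes that many women regard pregnancy as part of normal healthy life, so ratings near 100 are plausible for some. All of this stands, and it makes the bias conditional.

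It does not remove the gap in the data. A value from the earlier model would be the same for every woman, while the analysis is meant to rest on her own ratings.

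Importance can also be overstated. The model comparison is not listed among the primary or secondary outcomes, and the primary threshold, the willingness proportions and the ratings as collected are sound. That stands too. Nor is the gap wholly beyond repair after the interviews: a stated reference with a sensitivity range would help, although it would not be specific to the woman.

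On the comparator, the Background treats the probability trade-off as a direct choice method, so the threshold could be read as the stated choice. Moreover, the break-even varies little with baseline: with ratings 90, 88 and 40 it is 0.96 × 2/48 = 4.0, 0.90 × 2/48 = 3.75 and 0.84 × 2/48 = 3.5 per 100. The mismatch is therefore mainly one of unlike quantities, an option against a threshold, and calls for reconciling the wording.

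**Conclusion.** The point holds in a conditional form. It is certain from the text that no uncomplicated pregnancy without LMWH is rated, and that the rating of the whole treated pregnancy is used as the LMWH burden. The women's ratings alone therefore cannot give the increment due to LMWH. A bias against LMWH follows if the no-event branch is set to full health and women rate uncomplicated pregnancy below 100. Its size rests entirely on assumed ratings and a simplified tree: none at a rating of 100, and a shift from 3.5 to 21.0 fewer VTE per 100 at ratings of 90, 88 and 40, enough to reverse the preferred option. The article does not state the value used.

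The effect is confined to the personalized decision analysis and to the regression and correlations that use the LMWH utility, where differences in how women rate pregnancy itself can blur the relation with the threshold. The primary VTE threshold is not touched. This is a change worth making, not a flaw in the study's main result.

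**What to change.** Add one feeling-thermometer rating, an uncomplicated pregnancy without LMWH, with a short description in the style of the existing states. Use it as each woman's no-event reference in the decision model, and take the LMWH burden as the difference from it. Where interviews are already done, state the reference utility of that branch and show the results over a range of values, including 100.

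Reconcile the Abstract with the Analysis section. Compare the model's preferred option with the woman's choice in her real-life situation and in each of the three hypothetical scenarios. Compare the model's break-even reduction with the VTE threshold only at the 16 per 100 baseline.

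The cost is about one minute per interview, one state description and a few sentences of analysis text. No additional participants are needed.

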#### Check for consistency and understanding

After presenting the descriptions and recording patient responses, interviewers will review participant responses to the various exercises to check for consistency in the participant’s choice. When interviewers identify inconsistencies, they will offer participants a chance to review and change their responses, avoiding any suggestion that responses should be changed. The reasons for any apparent inconsistencies will be determined and recorded. Following this consistency check, interviewers will ask participants two standardized questions to evaluate their understanding of the information provided during the interview [Additional file 1: Appendix II]. Interviewers will also provide a rating of the extent to which they believe the respondents had a clear understanding of the questions and their confidence in this assessment.

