#### Direct choice exercises

We will determine each participant’s willingness to receive LMWH prophylaxis through direct choice exercises. Women will initially complete what we refer to as the real-life scenario, followed in order by hypothetical scenarios, the visual analog scale, the probability trade-off exercise, a review of their answers, and finally questions to examine their understanding their understanding of the scenarios. Use of decision boards will facilitate patient understanding of the direct choice exercises. Descriptions of each phase of the interview follow.

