The scatter plots of each of the participants’ utilities, as determined by the FT ratings of the health states, and the VTE thresholds will be examined to evaluate the relation between participant utilities and their VTE threshold. We will calculate Pearson’s correlations between each of the utilities for the health states and the threshold.

We believe that a lack of consistency in patient responses is the best way to detect a problem with individual patient understanding, which if it occurs frequently enough (i.e. > or = 25% of participants), may represent a problem in the way in which the information is being presented. Therefore, we will review consistency data after 10, 20, 30, and 40 women have been enrolled. We will also examine consistency data prior to these pre-specified points if there is concern about the level of inconsistency in patient responses. Table 4 contains frequencies of inconsistent responses, which would favor a review of the study scripts and presentation tools. We will also compare responses between women who are consistent and those who are inconsistent in their responses, even after they are provided with the opportunity to correct discrepancies in their responses. If the results differ between these groups, our primary analysis will include only those with consistent responses.

**Table 4 T4:** Guidelines for frequencies of inconsistent responses favoring review of study scripts and presentation tools

**Frequency of inconsistent response**	**%**	**Lower bound of 95% CI**
> or = 5/10	50.0	23.7
> or = 8/20	40.0	21.9
> or = 10/30	33.3	19.2
> or = 12/40	30.0	18.1

For all key analyses above, we will compare results and the pattern of responses in women who answer the “understanding” questions correctly and those who do not. A similar comparison will also be made according to the interviewer’s impression of patient understanding. If the results differ between women categorized as understanding and not understanding, our primary analysis will focus on women with an apparent high level of understanding.

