## Discussion

Producing guidelines for management of pregnant women with prior VTE is problematic because there is little reliable information in the literature to guide the value and preference judgments necessary for making recommendations. Clinical management is challenging because of the lack of a standardized approach to presenting information and eliciting patients' choice. Our study will be the first to explore the preferences of women at risk of pregnancy-related VTE with respect to the use of antithrombotic therapy.

Our study has several strengths. We will address some of the limitations of the previous studies in the field of decision-making. These studies using direct choice methods, and in particular the probability trade-off, have shown many extreme choices that raise doubts about whether all patients understood the decisions they were making [84,88]. We pilot-tested standardized scripts that were reviewed by expert and non-expert clinicians, and allied health professionals to ensure appropriate readability and understandability. We are presenting probability information in three different ways. We have trained research assistants and will undertake quality control of the data as it accumulates.

We will check for consistency in the participants’ choice to either take or not take LMWH for a given probability of DVT. Participants will have discrepancies brought to their attention and will have the opportunity to change their responses. We will use standardized questions to test understanding of the information presented and the interviewer will provide a rating of the extent to which she or he believes the respondent had a clear understanding of the questions and their confidence in this assessment. Our analysis will include an exploration of whether patterns of responses differ (1) between those with an apparently high level of understanding and those who do not, (2) between those whose answers are consistent and those with inconsistent answers, and (3) between those who, according to the interviewer’s impression of patient understanding, show a correct understanding and those who do not. Finally, our multicenter international design limits the influence of local views about the use of LMWH prophylaxis for prevention of recurrent pregnancy-associated VTE and enhances generalizability.

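### As worded, an understanding rating given by the interviewer who already knows the VTE threshold can redefine the primary analysis population, and so can select women on the outcome

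*Protocol article*

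**What the plan says.** Four places in the protocol article bear on this.

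- **Probability trade-off.** The interviewer elicits the primary outcome: "The interviewer will systematically vary the risk of VTE with LMWH prophylaxis".
- **Direct choice exercises.** The interview ends with "the probability trade-off exercise, a review of their answers, and finally questions to examine their understanding".
- **Check for consistency and understanding.** First, "interviewers will review participant responses to the various exercises to check for consistency". Then, "Following this consistency check, interviewers will ask participants two standardized questions to evaluate their understanding". The rating is described last: "Interviewers will also provide a rating of the extent to which they believe the respondents had a clear understanding of the questions". Interviewers also record how confident they are in it.
- **Primary and secondary outcome(s).** Key results are compared between women who do and do not answer the standardized questions correctly. Next comes: "A similar comparison will also be made according to the interviewer’s impression of patient understanding". The following sentence says that, if results differ by category of understanding, "our primary analysis will focus on women with an apparent high level of understanding".

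The Discussion adds, about earlier trade-off studies, that they "have shown many extreme choices that raise doubts about whether all patients understood the decisions they were making".

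**The concern.** The rater is not independent of the outcome. She has just established the woman's threshold and gone over it with her, and the rating records what she believes rather than a score against a key. If a surprising threshold lowers her opinion of the woman's understanding, even occasionally, the low-rated group will differ on the threshold for that reason alone. That difference is what the rule treats as grounds for moving the primary analysis to the other group.

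This is a separate matter from the restriction being triggered by the data. Even a restriction fixed in advance would select on the outcome if the classifier was formed with the outcome in view.

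At stake is the primary mean threshold. The study exists to measure preferences, including strong ones, and a comparison by interviewer impression cannot by itself separate misunderstanding from an unusual but genuine preference.

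**Working it through.** The plan gives no figure on this point, so there is none to reproduce. The check has two parts.

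**1. Does the text allow it?**

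- Rater knows the outcome: yes. The order of steps puts the rating last. That timing is inferred from the order of the text, but the interviewer runs the trade-off in any case.
- Rating is subjective: yes. The text shown gives no blinding, independent rater or rating criterion.
- Rating can affect the primary population: yes, as worded. The restriction sentence directly follows the interviewer-impression comparison and is not limited to the standardized questions.

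**2. How large could the effect be?**

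The 0 to 16 scale and n = 100 come from the Sample size section. Everything else is assumed: the spread of thresholds, the low-rating probabilities, and true understanding being unrelated to the threshold.

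If group g has share p, mean m and probability f of a low rating, the mean among retained women is

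Σ p(1 − f)m / Σ p(1 − f).

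*Extremes at the high end only.* Take 15% of women at 14–16 (mean 15) and 85% evenly spread over 0–12 (mean 6), with f = 0.05 for the latter.

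- All women: 0.15 × 15 + 0.85 × 6 = 7.35.
- f = 0.3 for extreme women: (0.105 × 15 + 0.8075 × 6) / 0.9125 = 6.42 / 0.9125 = 7.04, a shift of −0.31.
- f = 0.5: (0.075 × 15 + 0.8075 × 6) / 0.8825 = 5.97 / 0.8825 = 6.76, a shift of −0.59.
- Variance with whole-number thresholds: 0.85 × 14 + 0.15 × 0.67 + 0.15 × 0.85 × 9² = 22.33, so SD = 4.73 and the 95% half-width is 1.96 × 4.73 / 10 = 0.93. The shifts are about a third and just under two thirds of that.

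These are means if restriction always happens. In simulation the two groups differed at p < 0.05 in about 56–59% (f = 0.3) and 90% (f = 0.5) of studies, against about 5% when the rating ignored the answer.

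*Applying the conditional rule.* A second simulation (20,000 studies per setting) restricted only when a Welch t statistic exceeded 1.98. That cut-off is an assumption, because the plan does not define a difference. Women who were not extreme had a mean of about 5 and f = 0.10.

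| Share at 16 / at 0 | f, extreme | Mean, all women | Always restrict | Conditional rule | 95% CI coverage under rule |
|---|---|---|---|---|---|
| 20% / 0% | 0.3 | 7.20 | 6.78 | 6.93 | 88% |
| 20% / 0% | 0.5 | 7.20 | 6.34 | 6.38 | 57% |
| 10% / 0% | 0.3 | 6.10 | 5.87 | 6.01 | 92% |
| 10% / 0% | 0.5 | 6.10 | 5.64 | 5.76 | 80% |
| 10% / 10% | 0.3 | 5.60 | 5.49 | 5.58 | 94% |
| 10% / 10% | 0.5 | 5.60 | 5.36 | 5.52 | 93% |
| 5% / 20% | 0.3 | 4.55 | 4.63 | 4.60 | 95% |
| 5% / 20% | 0.5 | 4.55 | 4.72 | 4.63 | 95% |

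The formula reproduces the second row: (0.10 × 16 + 0.72 × 5) / 0.82 = 6.34.

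*Balanced extremes.* With 7.5% or 10% of women at each of 0–2 and 14–16, and the rest even over 2–14, the extreme women average (1 + 15) / 2 = 8, the same as the others. Dropping them cannot move the mean on average. Simulated bias was below 0.01, with coverage of 94–95%.

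*Rating unrelated to the answer* (f = 0.15 for all, in the settings of the table): bias about 0.01, coverage 94–95%.

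The bias therefore needs two things together: a rating that tracks the answer, and extreme answers mostly at one end.

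**The case against.** **The protocol does not tell interviewers to mark down extreme answers.** This stands. A reader might infer from the Discussion that the plan itself treats an extreme threshold as misunderstanding. That remark concerns earlier studies, and the remedies listed are piloted scripts, several presentation formats, training, quality control and standardized questions. The plan's own stated marker of poor understanding is inconsistency. The remark makes a rating influenced by the answer plausible, no more.

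**The rating may not be meant to drive the restriction.** The Discussion lists the interviewer's impression separately from an apparently high level of understanding, which is the term the restriction uses. The restriction is also worded as a focus, whereas the parallel rule for inconsistent answers includes only consistent women. So the intent is ambiguous. In the analysis section, however, the natural reading covers both classifiers, and nothing there says which one decides.

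**The harm depends on one-sided inputs.** This also stands. A reader might infer that the primary mean will be pulled down by 0.3–0.6. The documents give neither the distribution of thresholds nor interviewers' rating behaviour. Balanced extremes give almost no bias, and more women at 0 reverse its sign.

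**Unseen material may help.** The appendix and interview materials may hold rating anchors. Anchors would reduce the subjectivity but would not remove the rater's knowledge of the threshold.

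**The two questions have the same weakness.** The same interviewer asks them, after the answers are known. But the wording is standardized and the analysis classes women by whether they answered correctly, which leaves less room for the threshold to influence the result.

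**Conclusion.** The concern holds as a defect in the stated rule. A subjective rating, made by someone who knows the primary outcome, can help decide who is in the primary analysis. It does not show that the rating will be biased, or that the reported mean will move in a particular direction.

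The size rests wholly on assumed inputs. It is near zero if extreme thresholds balance. If 15% of women lie at the high end and 30–50% of them are rated low, it is about 0.3–0.6 per 100 when restriction always happens. The other one-ended settings examined give 0.23 (6.10 − 5.87) to 0.86 (7.20 − 6.34) when always restricting, and 0.09 to 0.82 on average under the conditional rule as modelled. The change is worth making because it is cheap and the possible effect is not negligible beside the interval width. An experienced rater might never be swayed, but the plan as written could not show that.

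**What to change.** In the analysis section, where the restriction for understanding is stated, add that the interviewer's impression does not define the population of the primary analysis. Then take one of two routes:

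- base any restriction for understanding only on the two standardized questions; or
- keep all women in the primary analysis and report the restricted set as a sensitivity analysis.

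In either case, report results by interviewer rating descriptively, for example the mean threshold at each rating level.

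The cost is a sentence or two, with no new data and no change to the interview. The downside is that two questions may miss misunderstanding that an interviewer would notice. The descriptive or sensitivity analysis by rating would show whether that matters.
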